### Study aims, objectives and hypothesis

The BOOSt study aims to determine the:feasibility of establishing Birthing on Country services, inclusive of birth centres, in urban and rural settingsacceptability of the new Birthing on Country services for women and families, Communities and health service providersclinical and cultural safety of the new servicesclinical and cost-effectiveness,key processes required to establish Birthing on Country birth centres and to create sustainability.

The primary hypothesis is that maternity care from a Birthing on Country service will improve maternal and newborn outcomes for First Nations mothers and babies, when compared to historical controls and a standard care cohort (where available).

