### Outcome measures

#### Primary maternal outcomes

First antenatal visit^3^ in the first trimester (< 14 weeks) [for definition please see p. 5 [52]]Total number of antenatal visits (either 0–4, or > =5)Normal birth (> = 37 weeks, vertex presentation, spontaneous onset of labour, no regional analgesia, spontaneous vaginal birth, no episiotomy)

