#### Power and sample sizes

BOOSt has been powered to detect a clinically significant change in preterm birth [53]. Preterm birth rates for First Nations babies in the Illawarra Shoalhaven Local Health District have been reported over a recent 5 year period as between 10.3 and 17.5%, average 12.9%. Based on our observations in the IBUS study [19], we propose a minimum treatment effect of 50% reduction (Odds ratio OR 0.5) for the preterm birth rate in the innovation arm. During recruitment, we will aim to access routinely collected maternity data for approximately 687 women at the rural site and 614 from the urban site (based on an estimated 20% attrition rate). From commencement of the new model of care, we will aim to obtain data from a minimum of 296 births (rural site) and 264 (urban). Given small numbers in the rural site (~ 120 births of First Nations babies attending Birthing on Country per year) and a ~ 3.5 year post-intervention study timeframe, we estimate 70% of the total sample to be in the pre-intervention group and 30% post-intervention. To detect this difference with 80% power and a type 1 error of 5%, and factoring exclusions for ~ 7% twin babies/babies with fetal anomaly, and 10% missing data, 983 women/births in total are needed, which includes 687 in pre-intervention and 296 in post-intervention groups. This sample size will also enable enough power for primary infant and maternal outcomes. For the urban site, the required sample size would be 878: 614 in pre-intervention and 264 in post-intervention groups. For the sub-studies, the sample size will be determined according to qualitative research conventions and considerations around data saturation.

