#### Quantitative data

##### Health services and other routinely collected data

Anonymous data from all women attending the site hospitals and health services during the study period will be extracted and analysed by birth model of care. Quantitative analyses will compare maternal and infant health outcomes between the baseline cohort (both sites) and Birthing on Country service innovation cohort (both sites), as well as standard care/concurrent and historical control groups, and non-First Nations groups (where available).

The clinical and costing outcomes data will be derived from routinely collected electronic healthcare databases at each site. Data will be imported to Stata® or Statistical Package for Social Sciences (SPSS®). While data will initially be re-identifiable (with unique study number) all patient identifiers will be removed. Data cleaning and coding decisions will be documented.

Analysis will be performed with the latest version of the appropriate software and statistical significance will be determined at the 0.05 level. Binary outcome measures will be presented using odds ratios with 95% confidence intervals. Several methods will be used to address selection bias e.g. multivariate logistic regression models, linear regression models, propensity score matching (identifies and controls for confounders e.g. the presence of pregnancy complications), and multilevel modelling controlling for clustering factors. Longitudinal outcomes will be analysed with generalized estimating equations to account for the correlation between observations repeated in the same person. We will use trend analysis to compare rates of preterm birth between First Nations and non-First Nations women, which will demonstrate if this inequity has reduced.

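### Six outcomes are primary at a single 0.05 level with no success rule, while the sample size allows for one unadjusted test, that of preterm birth

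*Protocol article*

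**What the plan says.** Under Study aims, objectives and hypothesis, the primary hypothesis is that "maternity care from a Birthing on Country service will improve maternal and newborn outcomes". No outcome is singled out and no number of successes is required.

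Under Primary maternal outcomes the article lists a first antenatal visit before 14 weeks, the visit count ("Total number of antenatal visits (either 0–4, or > =5") and normal birth. Under Primary infant outcomes it lists preterm birth, healthy baby and exclusive breastfeeding at discharge. That makes six primary outcomes.

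Under Health services and other routinely collected data, "statistical significance will be determined at the 0.05 level". The article gives no hierarchy or allocation of alpha among the six.

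Under Power and sample sizes, "BOOSt has been powered to detect a clinically significant change in preterm birth", and the 80% power and 5% type 1 error are attached to that one difference. The section then adds: "This sample size will also enable enough power for primary infant and maternal outcomes". No rate, effect or calculation is given for the other five outcomes.

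**The concern.** A single broad hypothesis, six primary outcomes and one significance level leave the authors free to decide after the event which result counts. A gain in antenatal visits alone could be presented as confirming the hypothesis while preterm birth, the outcome the study was sized for, shows nothing. Whether the 5% used in planning protects against this depends on two things: whether the sample size contains an allowance for several tests, and what counts as success. The second is not stated.

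**Working it through.** **1. Reproduce the rural sample size.** The inputs come from Power and sample sizes:
- Control rate: "between 10.3 and 17.5%, average 12.9"%.
- Effect: "we propose a minimum treatment effect of 50% reduction (Odds ratio OR 0.5) for the preterm birth rate in the innovation arm".
- Split: 70% pre-intervention and 30% post-intervention, so r = 3/7.
- Power 80%, type 1 error 5%. Sidedness is not stated and is taken as two-sided.
- Losses: about 7% exclusions and 10% missing data.

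The two-proportion formula without continuity correction is

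n(pre) = [1.960·√((1 + 1/r)·p̄(1 − p̄)) + 0.842·√(p1(1 − p1) + p2(1 − p2)/r)]² / (p1 − p2)²

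with p1 = 0.129, p2 = 0.0645 and p̄ = 0.7 × 0.129 + 0.3 × 0.0645 = 0.10965. The first term is 1.118 and the second 0.423, so n(pre) = (1.541)² / 0.00416 ≈ 571.2. This rounds up to 572, with 246 post-intervention, 818 evaluable in all. Inflated, 818/(0.93 × 0.90) = 977, or 818/0.83 = 986. The article states 983.

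The figure therefore rests on one test at an unadjusted 0.05 and on a halving of risk. Taken literally as an odds ratio of 0.5 (12.9% to 6.89%), the same formula gives 959 evaluable and 1,146 to 1,155 after inflation, which does not match.

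**2. Error rate if any one of six may confirm the hypothesis (assumption).** Under independence, 1 − 0.95⁶ = 0.265. By definition the outcomes are not independent: normal birth and healthy baby both require at least 37 weeks, so both overlap with preterm birth. The true correlations are not in the document. Simulating six two-sided normal tests with an assumed common correlation gives:

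| Correlation | Chance of at least one false positive |
|---|---|
| 0.3 | 24% |
| 0.5 | 21% |
| 0.7 | 16% |
| 0.9 | 11% |

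If all six had to succeed, the error would not exceed 5%, but power for the hypothesis would be no higher than for its weakest outcome.

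**3. What splitting alpha would cost.** At 0.05/6 = 0.00833, the same preterm birth comparison needs 1,278 evaluable births, or 1,527 to 1,540 after inflation, against 983. The planned sample would have about 53% to 54% power for preterm birth instead of 80%. If preterm birth alone is confirmatory, alpha stays at 0.05 and the sample size stays at 983.

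**4. The power statement for the other five.** Evaluable rural births are about 687 × 0.837 = 575 and 296 × 0.837 = 248. The baseline rates below are assumptions, because the article gives none; tests are two-sided at 0.05. The two odds-ratio rows use the 572 and 246 from step 1.

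| Scenario | Result |
|---|---|
| Odds ratio 2, baselines 30% to 70% | 97% to 99% power |
| Odds ratio 1.5, baselines 30% to 70% | 63% to 75% power |
| Gain of 5 percentage points, baselines 30% to 80% | 26% to 39% power |
| Difference detectable with 80% power, baselines 30% to 80% | about 8 to 11 percentage points |

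**The case against.** Several points on the other side are sound.

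- **A reader might infer that the article claims 5% for the primary hypothesis and that this claim fails.** It does not make that claim. The 5% is attached to the preterm birth difference, and there it holds.
- **A reader might infer that any one of the six satisfies the hypothesis.** The wording is plural and carries no success rule, so this is one reading among several. Every figure in step 2 depends on it.
- **The 26.5% is a ceiling.** Overlapping definitions rule out independence, so it should not be the headline.
- **A reader might infer that the sufficient-power statement is false.** It is unsupported, not refuted: for an effect as large as the odds ratio assumed for preterm birth it would be met at most plausible baselines, and for modest gains it would not.
- **Testing at each site separately would mean twelve tests**, 1 − 0.95¹² = 46% under independence. The two sites are sized separately, but the article does not say they are tested separately, so this does not count towards the finding.
- **Multiplicity methods are commonly left to the analysis plan, and this is a condensed article.** An absent adjustment method alone would be no finding.

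The last point does not dispose of the matter. Primary status, the hypothesis, the 0.05 level, the sizing and the power statement are all fixed in this text. An alpha split added in an analysis plan would undercut the stated sample size. Naming one confirmatory outcome there would change what the primary list here means. Either way the article needs a statement.

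**Conclusion.** The point holds in a limited form. Six outcomes share primary status, one hypothesis and one 0.05 level without a success rule, while the sample size provides for a single unadjusted test of preterm birth. That test keeps its 5%. Under the assumed any-one-succeeds reading, the chance of at least one false-positive primary outcome is about 11% to 24% for assumed equal correlations of 0.9 to 0.3, and at most 26.5%. So even strongly correlated outcomes would give roughly twice 5%. The statement that power is sufficient for the other five cannot be checked from the document and depends heavily on the effect assumed. This should be corrected. It does not invalidate the sample size or the preterm birth analysis.

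**What to change.** Before outcome analysis, designate preterm birth as the single confirmatory outcome at two-sided 0.05. The sample size of 983 (rural) is unchanged, and so is the 878 given for the urban site. The other five can stay listed as important outcomes, reported either with Holm-adjusted p-values or as estimates with confidence intervals and no confirmatory claim.

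Replace the sentence on sufficient power with the difference each of the other five outcomes can detect at the planned size, stating the baseline rate assumed for each.

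The cost is wording in the protocol and the registry, with no extra births. There are two downsides. The other five outcomes carry a weaker claim. And because the cohort data run from 2013 to 2022 and the article appeared in January 2023, the re-ranking comes late and could look like selection after the event. It should therefore be dated, disclosed in the registry, and accompanied by a statement of whether any outcome data had been seen.

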## Background

With more than 200 years of colonisation in Australia, maternal and infant health disparities are frequently reported for First Nations families compared with non-First Nations [1]. The maternal mortality rate is between 3 and 5 times higher for First Nations women, and other perinatal indicators show stark discrepancies, including preterm birth (14% versus 8%), low birth weight (12% versus 6%) and perinatal deaths (12 versus 9 per 1000 births) [2].

While perinatal mortality is relatively rare in Australia overall, preterm birth and low birth weight are much more common. Reducing preterm births is an international priority, since it is associated with factors influencing poor health in the short- and long-terms, including adult chronic diseases [3]. Many factors associated with preterm birth are also considered modifiable. Known risk factors include maternal psychosocial stress [4], antenatal infections [5], cigarette smoking in pregnancy [6] and exposure to environmental tobacco [7], low/high body mass index [8], lower maternal education and young maternal age [9] among others.

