Workforce strategy	No specific pathways to support First Nations MIH workforce.	Supportive career pathways with First Nations MIH workers embedded in the team with cadetships (or similar) to support midwifery education for First Nations persons. Aboriginal Family Support Workers (or similar) work side-by-side with midwives.
Continuity	No continuity of midwifery carer through antenatal, intrapartum and postnatal continuum. Care is fragmented and women see multiple providers.	Continuity of midwifery carer networked from community to a higher-level service, offering 24/7 care from a named midwife from first presentation in pregnancy until handover to child health services 6 weeks after birth. Midwifery Group Practice (caseload) midwife providing clinical care in collaboration with the extended workforce based on need (e.g. psychologist, social worker, obstetrician, paediatricians, sexual and reproductive health).
Strengthening family capacity	No maternity programs focussed on strengthening family capacity and/or cultural connection in relation to services offered through this hospital. Women may enrol in external programs.	Programs that focus on strengthening family capacity and cultural connection in relation to MIH, integrated with the BoC service.
Place of birth	No out-of-hospital option. Hospitals do not recognise or incorporate the knowledge, values and birth aspirations of First Nations people.	During the first and second phase of the new care model, all intrapartum care will occur in hospitals. If feasible, a free-standing, community-based birth centre will be set up and available for First Nations women with uncomplicated pregnancies (Category A according to consultation and referral guidelines) [18]; women with complex pregnancies (Category B or C) will birth in the local or tertiary hospital. Birth care will incorporate traditional practice; recognise the connection with Land and Country; incorporate holistic health; value both First Nations and non-First Nations ways of knowing, learning and risk assessment; and will provide a culturally competent service.

Note: *MIH* Maternal and Infant Health

^a^Some sections reproduced from Kildea, Gao et al. [19] Permission not required under licence CC BY-NC-ND 4.0

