34	**Mean cost of care per mother/infant pair** Health economic evaluation takes a health system perspective and will conduct a cost-effectiveness analysis. Costs to be included are antenatal care, birth, postnatal care costs; readmissions costs within 6 weeks postpartum; infants’ special care nursery and readmission.		First AN visit	Until 6 weeks (mother) 28 days (baby)			

Key: *DC* Discharge (from hospital/birth centre etc), *MEDREC* Medical/maternity/obstetric records, *QUAL* Qualitative data collected via audio recorded, one-to-one yarns (a type of narrative interviewing), unstructured/semi-structured interviews, yarning circles (a type of focus group discussion), researcher field notes, *Sd* Standard deviation, SUR Questionnaires (surveys) designed for this study, *Wk* week

Notes

1. All tools/scales will be scored according to their recommended guidelines and outcomes reported accordingly

2. All items measured for both intervention and standard care groups

3. The time period under consideration for the innovation is from the first day of pregnancy until handover to child health services at 6 weeks postpartum, however the study is longitudinal following mothers and babies until 6 months

4. Please see Additional File 2 for more detail on scales and tools used in women’s surveys

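### Pregnancy complications are named as a matching confounder with no limit to those present at or before entry to care, so the match can condition on consequences of the service

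*Protocol article*

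**What the plan says.** Under the heading on health services and other routinely collected data, the protocol article introduces its adjustment methods: "Several methods will be used to address selection bias e.g. multivariate logistic regression models, linear regression models". The list goes on to "propensity score matching (identifies and controls for confounders e.g. the presence of pregnancy complications" and to multilevel modelling. Pregnancy complications are the only confounder that the analysis section names. No timing and no list of conditions is attached, and no method is called primary.

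The exposure starts early. Table 1 describes continuity of midwifery carer as "offering 24/7 care from a named midwife from first presentation in pregnancy until handover to child health services 6 weeks after birth". Note 3 to Table 2 says: "The time period under consideration for the innovation is from the first day of pregnancy until handover to child health services at 6 weeks postpartum".

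On the outcome, the power section states: "BOOSt has been powered to detect a clinically significant change in preterm birth". The Background says "Many factors associated with preterm birth are also considered modifiable" and continues "Known risk factors include maternal psychosocial stress [4], antenatal infections [5], cigarette smoking in pregnancy [6".

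**The concern.** A confounder must not be a consequence of the exposure. A complication that arises after a woman has entered the service falls inside the exposure period as the article defines it. If the service prevents some complications, and fewer complications mean fewer preterm births, then matching women on complications removes that part of the benefit from the estimate. What remains is the effect that does not pass through complications, whereas the hypothesis concerns the total effect of the care model.

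Recording is a second route to bias. Timing of the first visit and number of antenatal visits are both primary maternal outcomes. If the service changes contact, it can change what is diagnosed. More contact could bring milder complications into the recorded group, and matching on the record would then favour the new service.

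The outcomes at stake are preterm birth, on which the study is powered, and the two composites, healthy baby and normal birth. Both composites require at least 37 weeks' gestation.

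**Working it through.** **1. Order in time.**
- Exposure: from first presentation (Table 1) or from the first day of pregnancy (Table 2, note 3).
- Matching variable: presence of pregnancy complications, with no time limit.
- Outcome: preterm birth, at delivery.

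Read as written, the match admits variables that arise between exposure and outcome. Nothing in the article separates conditions present at entry from later ones.

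**2. A plausible path.** The Background names stress, antenatal infections and smoking in pregnancy as risk factors for preterm birth and regards many such factors as modifiable. The section on women's yarns and interviews plans to explore how care relationships affect behaviours such as smoking cessation. The article does not state that the service works by preventing complications, so this path is an inference.

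**3. The planned effect, reproduced first.** Inputs from the power section: control risk 12.9%, 50% reduction, 80% power, 5% type 1 error (two-sided assumed), 70:30 allocation, about 7% exclusions and 10% missing data. The two-proportion normal approximation without continuity correction, 12.9% against 6.45%, gives 572 + 246 = 818. Inflation gives 818 / (0.93 × 0.90) = 977, or 818 / 0.83 = 986. The stated total is 983, so the rural figure is reproduced with the reduction read as a risk ratio. Read as an odds ratio of 0.5 (12.9% to 6.89%), the inflated total would be about 1146. The illustration therefore uses 12.9% to 6.45%.

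**4. Illustration.** Let *s* be the share of the risk reduction that passes through complications. It is an assumption; the documents give no value. After matching on complications, the comparable control risk is

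p_c = 0.129 − s × (0.129 − 0.0645)

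and the odds ratio is [0.0645 / 0.9355] / [p_c / (1 − p_c)]. Power is for the net sample after exclusions and missing data: 687 × 0.837 = 575 and 296 × 0.837 = 248.

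| s (assumed) | matched control risk | odds ratio | power |
|---|---|---|---|
| 0 | 12.90% | 0.47 | 80% |
| 25% | 11.29% | 0.54 | 58% |
| 50% | 9.68% | 0.64 | 31% |
| 75% | 8.06% | 0.79 | 11% |
| 100% | 6.45% | 1.00 | 2.5% |

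The power column assumes that matching discards nobody. With the planned effect read as an odds ratio of 0.5, the corresponding values at 25, 50 and 75% are 0.58, 0.67 and 0.81, so the pattern does not depend on that reading. The table covers mediation only; bias from differential recording is not in it.

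**The case against.** The wording is an example inside a list of examples. Matching is one of several approaches, none is primary, and the full covariate list may stand in an analysis plan that is not shown. That limits how far the sentence commits the study. But the point is not that a list is missing: the article itself labels as a confounder a variable that the service can change, and an analysis plan that followed it would carry this forward.

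A reader might infer that the named variable is by its nature post-exposure. The text does not say so. Conditions already present at first presentation are ordinary baseline confounders, above all against concurrent standard care, where case mix may differ.

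A reader might also infer that matching would wipe out the effect. An example can be built to show this. Assume complications in 30% under standard care and 20% under the service, with preterm risk 25% with and 7% without a complication in both groups. Then 0.30 × 25% + 0.70 × 7% = 12.4%, and 0.20 × 25% + 0.80 × 7% = 10.6%, a risk ratio of 0.855 that becomes 1.00 within strata. But equal stratum risks in both groups assume full mediation, so the result is built in. Set against the planned fall of 6.45 points, the same shift of 1.8 points is 1.8 / 6.45 = 28%. The odds ratio would move from 0.47 to about 0.55 (matched control risk 12.9% − 1.8% = 11.1%). That is attenuation, not disappearance.

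Finally, complications may also act on selection. Data are to be analysed by birth model of care. Table 1 says that, if a birth centre opens, "women with complex pregnancies (Category B or C) will birth in the local or tertiary hospital", and Table 2 (item 33) counts transfers out of the birth centre or model of care. If later complications influence the model in which a woman gives birth, dropping them leaves some confounding. This stands, and the fix has to address it.

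**Conclusion.** The point holds in limited form. The article names a matching variable without a time limit, while its own definition of the exposure places later complications after exposure. Matching on those would bias the total effect on preterm birth, healthy baby and normal birth. The probable direction is toward the null, but differential recording could push the other way.

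The bias arises only if the service changes complications or their recording, or if complications share unmeasured causes with the outcome. Its size cannot be derived from the documents. The figures of 0.54 and 0.64 in place of 0.47 rest on assumed mediated shares of 25% and 50% at the planned effect. The text does not support saying that every pregnancy complication is a mediator, that the whole effect would be lost, or that the matched estimate is the one on which the study will rest.

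**What to change.** Reword the example to: *pre-existing conditions and obstetric history present at or before first presentation*. In the main effect analysis, restrict propensity and regression covariates to such characteristics where the routine records hold them, for example age, parity, previous preterm birth, pre-existing diabetes or hypertension, and site. The article does not list the extracted variables, so availability must be checked.

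Use complications that develop or are diagnosed later only as outcomes, or in a labelled mediation or sensitivity analysis. Smoking at the first antenatal visit needs care because it is a listed secondary outcome (Table 2, item 5). It should not enter the main adjustment without a note to that effect.

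The cost is one sentence of wording. The small downside is residual confounding in the concurrent comparison if later complications influence the model of care in which a woman gives birth. Assigning women to the model of care they entered, rather than the one in which they gave birth, limits this.
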